### Safety Assessment

The safety of the Ayush interventions was determined by recording the incidence of AEs, if any, during scheduled follow-up visits in a structured format. All AEs during the study were recorded and monitored as per ICH (International Council for Harmonisation of Technical Requirements for Pharmaceuticals for Human Use) Good Clinical Practice guidelines. Safety was also evaluated by assessing liver function tests, kidney function tests, and lipid profiles on days 60 and 120 from baseline.

### Sample Size

Based on the findings from a previous study on similar conditions, the anticipated incidence of AMS within the CG was 25%, while the assumed incidence in the AG was 18% [7]. To achieve a statistical power of 90% and a CI of 95%, an initial sample size of 722 per group was calculated. Accounting for an expected attrition rate of 15%, the final sample size for each group was determined to be 830 participants (N=1660 in total). The sample size of 1660 participants was stratified into stage I high altitude and stage II high altitude. A total of 830 participants were included from stage II high altitude, while the remaining 830 were from stage I high altitude. The participants studied at each of the 2 altitude stages were randomly allocated to the AG and CG.

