### Randomization

Block randomization with unequal block sizes randomly assigned participants to either the AG or CG with a 1:1 allocation to minimize predictability. Block randomization was implemented separately for stage I and stage II participants to ensure balanced allocation within each altitude-exposure setting. The SPSS version 28.0 (IBM) was used to generate the random number sequences. An independent statistician not involved in the participants’ enrollment and assessment generated the randomization sequence.

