### Statistical Methods

The categorical data will be presented as numbers (percentages) and compared between groups using the *χ*^2^ test, while within-group comparisons will be performed by using the McNemar or Cochran Q-test. Continuous data following a normal distribution will be reported as mean (SD), and between-group comparisons will be performed using an independent sample *t*-test. Within-group comparisons for normal data will be performed using a paired sample *t*-test/repeated measures ANOVA. Nonnormal data will be reported as median (first quartile, third quartile), and between-group comparisons will be conducted using the Mann-Whitney test. Within-group comparison will be done using the Wilcoxon signed-rank test or Friedman test. Baseline variables, such as age, prior altitude exposure, and hydration-related indicators, will be examined descriptively and adjusted in multivariable models where relevant. Regression analysis will be performed to study the effect of confounding variables on the incidence of AMS. The data of participants having early descent will be analyzed with censored data models. A *P* value less than .05 will be considered significant. The SPSS version 28.0 is being used for statistical analysis.

The modified intention-to-treat analysis approach will be applied to handle missing data. The missing data for all participants for whom data are available for at least one visit post-baseline will be imputed. The last observation carried forward method will be used for imputing the missing values.

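### Sample Size: the 15% attrition allowance was added as 722 × 1.15 = 830 per group rather than 722 / 0.85 = 850, so power at 15% attrition is about 89.3%, marginally below the stated 90%

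*Protocol article*

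**What the plan says.** The Sample Size section of the protocol article assumes an AMS incidence of 25% in the control group and 18% in the Ayush group. It asks for 90% power with a 95% confidence level, and reports that "an initial sample size of 722 per group was calculated". The next step is the one at issue: "Accounting for an expected attrition rate of 15%, the final sample size for each group was determined to be 830 participants (N=1660 in total". The formula for the attrition step is not given.

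The remaining inputs are in other sections. Under Randomization, the trial "randomly assigned participants to either the AG or CG with a 1:1 allocation". Under Statistical Methods, "The categorical data will be presented as numbers (percentages) and compared between groups using the" chi-squared test, and "A *P* value less than .05 will be considered significant". The article does not say whether the test is one- or two-sided.

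**The concern.** An attrition rate is ordinarily the share of enrolled participants who are lost. The enrolled number must then be the required evaluable number divided by one minus that rate. Multiplying by one plus the rate gives a smaller number, and the trial falls short of its evaluable target when the planned attrition occurs. The figure of 830 looks like the product of that multiplication.

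What is at stake is the accuracy of the power statement. Analysis is in progress and the results are unpublished, so the same sentence may be repeated in the results paper.

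**Working it through.** **Inputs.** From Sample Size: p1 = 0.25, p2 = 0.18, power 90%, 722 per group before attrition, attrition 15%, 830 per group after. From Randomization: 1:1 allocation. From Statistical Methods: chi-squared test, significance level .05. Two-sided testing is inferred from the 95% confidence level and from the fact that it reproduces 722.

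**Step 1: reproduce 722.** With p̄ = (0.25 + 0.18)/2 = 0.215, the two-proportion formula with pooled variance under the null and no continuity correction is

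n = [1.960 × √(2 × 0.215 × 0.785) + 1.282 × √(0.25 × 0.75 + 0.18 × 0.82)]² / 0.07² = 721.8, rounded up to **722**.

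This matches the article exactly. Other conventions do not: unpooled variance gives 719, arcsine 720, continuity correction 751, and a one-sided test 589. So 722 is the evaluable number needed for 90% power on the article's own assumptions.

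**Step 2: identify how 830 was reached.**
- 722 × 1.15 = 830.3, which matches the stated 830.
- 722 / 0.85 = 849.4, rounded up to 850 per group, or 1700 in total.
- Difference: 850 − 830 = 20 per group, or 40 in total; 20/830 = 2.4%.

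**Step 3: what 830 delivers.**
- Evaluable after 15% loss: 830 × 0.85 = 705.5 per group, against the 722 required.
- Largest attrition that still leaves 722: 1 − 722/830 = 13.0%.

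**Step 4: power for 25% against 18%, two-sided .05.**

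| Attrition from 830 per group | Evaluable per group | Power |
|---|---|---|
| 0% | 830 | 93.5% |
| 5% | 788.5 | 92.3% |
| 10% | 747 | 91.0% |
| 13% | 722 | 90.0% |
| 15% | 705 | 89.3% |

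The shortfall at 15% is 90.0 − 89.3 = 0.7 points. It hardly depends on the formula. With unpooled variance, power falls from 90.1% at 722 to 89.4% at 705; with a continuity correction, from 88.8% to 88.1%.

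**The case against.** The best case for leaving the sentence alone is that nothing of substance follows from it. A gap of 0.7 points is well inside the uncertainty about the assumed 18%. The full 15% also may not apply to the primary outcome. Under Outcome Measures, AMS is scored daily in the first 7 days at stage I and again in the first 4 days at stage II, which takes the study schedule to about day 10 of 120. Under Compliance With the Study Interventions, data collected before withdrawal are used. Under Statistical Methods, anyone with at least one post-baseline visit is kept and imputed. A participant who leaves on day 40 would still count in the primary comparison.

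Most of this stands. It shows that the effect is small and that 89.3% is the lower end for the primary outcome if 15% means loss over 120 days. It does not make the sentence right: the section applies 15% to this very calculation, and the article gives no early-attrition figure to put in its place. One could also read 15% as a simple uplift on 722, which would make 830 consistent. But that is not what an attrition rate normally means, and it corresponds to a loss of 0.15/1.15 = 13.0% of those enrolled.

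Two stronger inferences are tempting and are not supported. The first is that the trial is materially underpowered; the table above shows otherwise. The second concerns the number 830, which appears both as the size per group and as the number per altitude stage. A reader might infer that each stage was meant to have 90% power and does not. The article claims no stage-level power. It sizes the comparison by group, describes the total as stratified by stage, and reports the number per stage accurately. A stage-level power figure would also have to assume 25% against 18% at both altitudes, whereas the Introduction says that AMS becomes more frequent with altitude.

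**Conclusion.** The arithmetic error is real but minor. On the article's own inputs, 722 evaluable per group, 15% attrition, 830 enrolled per group and 90% power cannot all be true. The correct inflation gives 850 per group. With 830 and 15% attrition, about 705 per group remain and power is about 89.3%; 90% is kept only up to about 13% attrition.

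This rests on a two-sided 5% test without continuity correction, the stated 25% and 18%, and attrition read as a share of those enrolled. If the 15% is loss over 120 days, the 0.7-point shortfall is an upper bound for the primary outcome. How far below that bound the true shortfall lies cannot be determined from the article. The error does not bear on the validity of the primary comparison and supports no statement about power within a stage.

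**What to change.** Do not enrol more participants: the 1660 are enrolled and data collection is complete. Replace the attrition sentence in Sample Size with:

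> 830 per group (1660 in total) allows for about 13% attrition at 90% power; with 15% attrition the power is about 89%.

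Use the same wording in the results paper, and add no stage-specific power statement. The cost is one sentence and a very slightly less favourable power figure. Trial conduct and the planned analysis do not change.

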### Recruitment of Study Participants

During the study, the database of healthy personnel in high-altitude areas of the western Himalayan region was used to identify and recruit potential subjects. The investigators at the study site screened subjects based on the defined inclusion and exclusion criteria. The eligible participants were allocated to either of the 2 groups based on a computer-generated randomization schedule. The screening process was continued until the target sample size for the study was achieved.

### Randomization

Block randomization with unequal block sizes randomly assigned participants to either the AG or CG with a 1:1 allocation to minimize predictability. Block randomization was implemented separately for stage I and stage II participants to ensure balanced allocation within each altitude-exposure setting. The SPSS version 28.0 (IBM) was used to generate the random number sequences. An independent statistician not involved in the participants’ enrollment and assessment generated the randomization sequence.

### Allocation Concealment

Sequentially numbered, opaque, sealed envelopes were used to ensure allocation concealment. The participant’s enrollment number was printed at the top of the envelope, and a slip indicating the participant’s allocated group was kept inside. After completing all baseline assessments, the research staff provided the sealed envelope to the eligible participant. The participant opened the envelope and was then assigned to the group as indicated on the slip inside. The opened envelope and the printed slip were attached to the participant’s CRF for record and trial monitoring.

Participants assigned to the 2 study groups were housed in separate barracks throughout the study to prevent any protocol violations and minimize the risk of contamination bias. Further, yoga sessions and supplement distribution were conducted at designated areas accessible only to the intervention group, with attendance monitored by site instructors. The CG did not receive access to these sessions or materials, reducing the likelihood of unintentional participation. Study staff members were instructed to avoid sharing intervention-related information with control-group participants.

### Blinding

The study is open-label; however, to minimize any potential bias, the research staff assigned to assess the study outcomes will be blinded to the allocation of participants to the study groups. In addition, laboratory technicians analyzing blood samples were blinded through the use of coded specimens. The intervention team (Ayurveda practitioner and yoga instructor) had no role in outcome assessments, data entry, or laboratory procedures. The assessment team functioned independently and interacted with participants only at scheduled assessment time points. They were instructed not to inquire about participants’ allocation or intervention experiences. Each participant was assigned a unique study ID; all CRFs, questionnaires, and lab requisitions contained only this ID and not the allocation label. Further, statistical analysis will be conducted by an independent data analysis team not involved in intervention delivery or participant contact.

### Data Collection

The baseline demographics, clinical, and physical examination aspects were collected by qualified Ayush study personnel and reported in a CRF designed for this purpose. Subjective and objective outcome assessments were conducted according to the protocol (Table 3).

**Table 3. T3:** Study schedule.

	Screening	Baseline	Day 1 to 7	Day 10 (for participants at stage II HA^a^)	Day 30	Day 60	In case of early descent	Day 120
Written informed consent	✓							
Eligibility evaluation	✓							
Demographics and medical history		✓						
Clinical assessment	✓	✓	✓	✓	✓	✓	✓	✓
Vital parameters (resting heart rate, systolic and diastolic blood pressure, respiratory rate, SpO_2_^b^)	✓	✓	✓	✓	✓	✓	✓	✓
CBC^c^	✓			✓		✓	✓	✓
LFT^d^, KFT^e^	✓					✓	✓	✓
HbA_1c_^f^ and ECG^g^	✓							
Lipid profile		✓				✓	✓	✓
LDH^h^, CK^i^, CK-MB^j^, fibrinogen, aPTT^k^, prothrombin time, hs-CRP^l^, IL-6^m^, TNF-α^n^		✓		✓		✓	✓	✓
Lake Louise Scoring System for AMS^o^ assessment		✓	✓	✓				
Assessment for thromboembolic events						✓	✓	✓
DASS-21^p^, PSQI^q^, SF-12^r^ questionnaire		✓		✓		✓	✓	✓
Rescue medication			✓	✓	✓	✓	✓	✓
Assessment of adverse events			✓	✓	✓	✓	✓	✓
Assessment of drug compliance			✓	✓	✓	✓	✓	✓

a HA: high altitude.

b SpO_2_: peripheral capillary oxygen saturation.

c CBC: complete blood count.

d LFT: liver function test.

e KFT: kidney function test.

f HbA_1c_: glycated hemoglobin.

g ECG: electrocardiogram.

h LDH: Lactate Dehydrogenase.

i CK: creatine kinase.

j MB: myocardial band.

k aPTT: Activated Partial Thromboplastin Time.

l hs-CRP: high-sensitivity C-reactive protein.

m IL-6: interleukin-6.

n TNF-α: tumor necrosis factor-alpha.

o AMS: acute mountain sickness.

p DASS-21: Depression Anxiety Stress Scale-21 items.

q PSQI: Pittsburgh Sleep Quality Index.

r SF-12: 12-item short-form.

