## Introduction

### Background

High-altitude illness (HAI) is the collective term used for various debilitating health conditions that can affect individuals who are not acclimatized and ascend rapidly to high altitudes within 6 to 12 hours of their ascent to high altitude [1,2]. Conventionally, 2500 meters has been used as the threshold for HAI [2]. The spectrum of HAI encompasses various conditions that can range from mild to severe, among which the most typical are acute mountain sickness (AMS), high-altitude cerebral edema, and high-altitude pulmonary edema (HAPE). High-altitude cerebral edema and HAPE occur much less frequently than AMS but are potentially fatal. The risk factors for HAI are the rate of ascent, high altitude reached (especially the sleeping altitude), previous high-altitude exposure, and individual susceptibility [1,3,4]. AMS is a common clinical presentation in individuals venturing over 2500 meters and above [5]. The prevalence and severity of AMS rise with increasing altitude. It occurs in approximately 10% to 25% of nonacclimatized individuals at 2500 meters, which may increase to 50% to 85% at an altitude of 4500 to 5500 meters [2,6-8]. The pathophysiology of AMS includes relative hypoventilation, impaired gas exchange, increased sympathetic activity, fluid retention and redistribution, and raised intracranial pressure in case of moderate to severe AMS [1,5]. AMS presents with a group of nonspecific symptoms such as headache (primary defining symptom), gastrointestinal symptoms (anorexia, nausea, or vomiting), fatigue and/or weakness, dizziness, or disturbed sleep [9].

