### Outcome Measures

The primary outcome was the incidence of AMS, assessed using the 2018 Lake Louise Scoring System (LLSS). AMS is defined as an LLSS score of 3 or more points from the 4 rated symptoms (headache, nausea or vomiting, fatigue, and dizziness or light-headedness), including at least 1 point from headache [9]. The grading of LLSS score is mild AMS 3‐5 points, moderate AMS 6‐9 points, and severe AMS 10‐12 points [9]. The participants were assessed daily for the first 7 days at the stage I high-altitude areas using the LLSS score to record the incidence and evaluate the severity of AMS. The primary outcome will be reported as the proportion of participants who display symptoms of AMS and the proportion of participants with a score of more than 6 as per the LLSS. The participants enrolled for stage II were again assessed daily during their first 4 days at that altitude for the incidence and severity of AMS.

The secondary outcome measures included the proportion of participants who developed thromboembolic events (deep-vein thrombosis, pulmonary embolism, cerebral venous thrombosis, myocardial infarction, etc) during the study, change in the levels of markers of coagulation and hemostasis activation (total red blood cell count, hemoglobin, packed cell volume, D-dimer, lactate dehydrogenase, creatine kinase, creatine kinase-myocardial band, fibrinogen, activated partial thromboplastin time, prothrombin time), changes in the levels of proinflammatory markers (high sensitivity C-reactive protein, interleukin-6, tumor necrosis factor-α); self-reported changes in negative emotional states of depression, anxiety, and stress assessed through Depression Anxiety Stress Scale-21 item (DASS-21); change in sleep quality assessed through the Pittsburgh Sleep Quality Index (PSQI), and quality of life assessed through the 12-item short-form (SF-12) questionnaire. The secondary outcomes were evaluated on day 60 and day 120 from baseline. However, the participants enrolled for the stage II high-altitude area were also assessed on day 10 (day 4 of the AS at that altitude) and on the day of descent, in case of early descent before day 120.

Resting heart rate, systolic and diastolic blood pressure, respiratory rate, and oxygen saturation (SpO2) were also documented daily until day 7, alongside LLSS at stage I high altitude, and until day 10 in participants at stage II high altitude. These measurements were then taken on scheduled follow-up visits.

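### A participant who descends or is withdrawn for altitude illness inside the Lake Louise window, before a qualifying score, can be missed by the primary outcome and appear only as an adverse event

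*Protocol article*

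**What the plan says.** Outcome Measures defines the primary outcome as AMS by the 2018 Lake Louise score: at least 3 points over four symptoms (headache, nausea or vomiting, fatigue, dizziness), "including at least 1 point from headache". A severity proportion is reported as well. Scoring is daily for the first 7 days at stage I and again daily for the first 4 days at stage II.

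Table 3 (Data Collection) ticks "Lake Louise Scoring System for AMS^o^ assessment" at baseline, days 1 to 7 and day 10 for stage II. The column "In case of early descent" leaves that row blank. It does tick clinical assessment, vital signs with oxygen saturation, blood tests, thromboembolic events, the three questionnaires, rescue medication, compliance and "Assessment of adverse events". Reason for descent is not a row. Outcome Measures introduces the descent visit under the secondary outcomes, for stage II participants: "on the day of descent, in case of early descent before day 120".

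Three other sections bear on what happens next. Concomitant Care withdraws a participant with a serious or treatment-emergent adverse event. Compliance With the Study Interventions uses assessments completed up to withdrawal, with later data only if the participant consents. Statistical Methods sends early descents to censored data models and fills missing values by last observation carried forward.

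Background states "High-altitude cerebral edema and HAPE occur much less frequently than AMS but are potentially fatal". Outcome Measures names neither condition as an outcome.

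**The concern.** The people most likely to be brought down or withdrawn during the first days at altitude include those with the illness that the trial counts. If the last recorded score is below the threshold when they leave, nothing in the schedule obliges anyone to score them at the point of descent. The analysis rules then either carry the sub-threshold score through the rest of the window, making them non-cases, or censor them for a reason tied to the outcome, which is informative censoring.

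The severity component is exposed in the same way. Someone graded mild on the last daily score and then evacuated counts for incidence, but the worse grade is not recorded.

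The comparison at stake is AMS incidence and severity between arms. Equal loss mainly dilutes it. Unequal loss biases it, in a direction that cannot be predicted from the documents.

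**Working it through.** **1. The plan's own figure.** Inputs from Sample Size: 25% control, 18% Ayush, 90% power, 95% confidence (taken as two-sided 0.05), 1:1 allocation. With mean proportion 0.215,

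n = [1.960·√(2·0.215·0.785) + 1.282·√(0.25·0.75 + 0.18·0.82)]² / 0.07² = (1.139 + 0.742)² / 0.0049 ≈ 722 per group.

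This reproduces the stated 722, so the illustration below starts from the plan's own 90% power.

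**2. Following one participant through the sections.**
- Inside the window, the last daily score is below 3.
- Illness worsens before the next score, and the participant descends or is withdrawn (Concomitant Care).
- Table 3 asks for no Lake Louise score at that visit. Adverse events, clinical assessment and oxygen saturation are recorded.
- Data up to withdrawal are used unless more are consented to (Compliance With the Study Interventions).
- Carrying forward (Statistical Methods) keeps the value below 3 to the end of the window: a non-case. Under a censored model, follow-up stops because of the illness.
- Either way, the event is in the adverse-event data and not in the primary outcome.

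A descent score alone would not close the gap for pulmonary edema. The score has no respiratory item and needs a headache point, so pulmonary edema without headache cannot qualify.

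**3. Who is not affected.**
- Anyone with a qualifying daily score before descent: already a case for incidence.
- Anyone who descends after the window: no one is scored then, so the primary outcome loses nothing.

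**4. How much it could matter.** The article gives no rate of early descent, pulmonary edema or cerebral edema, so every rate here is an assumption. With n = 722 per group and p̄ the mean of the two observed rates p1 and p2,

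power = Φ{[|p1 − p2| − 1.960·√(2p̄(1 − p̄)/n)] / √[(p1(1 − p1) + p2(1 − p2))/n]}.

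Example, cases equal to 1% of participants lost in the control arm only: p1 = 0.24, p2 = 0.18, p̄ = 0.21. The numerator is 0.0600 − 0.0420 = 0.0180, the denominator is 0.0214, the ratio is 0.84 and power is 80.0%.

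| Assumed loss | Result |
|---|---|
| 2%, 5%, 10% of AMS cases, both arms alike | power 89.3%, 88.1%, 85.8% |
| 0.5%, 1%, 2% of participants (about 4, 7, 14 of 722), control only | power 85.6%, 80.0%, 65.3% |
| 0.5%, 1%, 2% of participants, Ayush only, both true rates 25% | rejection rate 5.6%, 7.3%, 14.4% instead of 5% |

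The last row uses 1 − Φ(1.960 − k/SE) + Φ(−1.960 − k/SE), with k the share lost and SE = √{[0.25·0.75 + (0.25 − k)(0.75 + k)]/722}. The two one-arm rows are extremes, because all the loss falls on one side.

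**The case against.** The case against is substantial, and most of it limits the point without removing it.

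- A reader might infer that the worst altitude illness leaves the trial uncounted. The documents do not support that. The early-descent column includes clinical assessment, oxygen saturation, rescue medication and adverse events. Safety Assessment records all adverse events, serious ones are notified within 2 working days, and a monitoring board reviews every 3 months.
- A reader might infer from Table 3 that a stage II participant who descends between day 7 and day 10 goes unscored. That follows only from a literal reading of the table. Outcome Measures and Data Collection both describe 4 days of scoring at stage II, and Outcome Measures says it is daily. A descent day inside the window is also a scoring day, though nothing ensures that the score comes before departure.
- The blank cell has a coherent origin. The early-descent column matches days 60 and 120 row for row, so it stands in for late follow-up, when no one is scored.
- Leaving pulmonary and cerebral edema out of the efficacy outcomes is a legitimate choice of endpoint. The objective is AMS, the two conditions are described as much rarer, and a history of pulmonary edema is an exclusion.
- One could divide an assumed 0.5% to 2% by the planned 7 points and report that 7% to 29% of the effect is at risk. That restates the assumption. It needs every such participant to lack an earlier qualifying score and all of them to be in one arm.
- Data collection ended in December 2023, so no visit can be changed.

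What remains is the participant who leaves the window ill and without a qualifying score. An adverse-event record does not correct the efficacy comparison, and neither carrying forward nor censoring recovers that score.

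**Conclusion.** The point holds in a narrow form. As written, the schedule and the analysis rules together allow a participant who descends or is withdrawn for altitude illness inside the scoring window, with no qualifying score yet, to be a non-case or to be informatively censored in the primary analysis, while the illness is recorded as an adverse event. It does not extend to later descents or to safety reporting.

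The size is unknown. The effect is small if few such cases occur or if they are spread evenly. It becomes material only if cases amounting to about 1% or more of participants are lost mainly from one arm, and nothing in the documents says that this happened. The reasoning takes the stage I window as 7 days, as in the Abstract, Outcome Measures and Table 3; one sentence in Data Collection mentions only the first day.

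The remedy is cheap, and the article says that analysis is still in progress, so the point is worth acting on.

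**What to change.** Keep the score-only analysis as primary. Before the arms are compared, specify a sensitivity analysis that counts descent or withdrawal for altitude illness inside the window (first 7 days, or first 4 days at stage II), including pulmonary or cerebral edema, both as AMS and as meeting the severity component. Identify these participants from the existing adverse-event, serious-event and clinical records, using reviewers who do not know the arm. Tabulate the events by arm and stage, stating how many already had a qualifying score.

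For any future use of the schedule, Table 3 should carry the Lake Louise score and the reason for descent at descents inside the window.

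The cost now is a blinded review of records already held, one extra analysis and one table. The downside is that the sensitivity outcome is broader than the score and depends partly on evacuation decisions in an open-label trial. It should therefore be reported beside the score-only result and not replace it.
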